#### Sample size calculation

The number of participants required to show statistical significance is based on previously published studies in which vascular function was assessed in HIV patients [50]. An error probability (α) of 0.05, and power (1 − β) of 0.80 and an average effect size (d) of 0.5 were used to calculate the sample size (n = 64 persons). Assuming a 25% drop out rate, we will use N = (64 + (64*25)/100) = 80 mothers/group to ensure that we will have enough sample size/group to show statistical significance. Total number of participating mothers will therefore be 160 (80 cases and 80 controls) and their offspring-160.

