#### Statistical analysis

Data analyses will be carried out using IBM statistical package for social sciences (SPSS) Version 23.0 (IBM Corp.). Armonk, NY, USA) and STATA. Data will be checked for normality using Shapiro-Wilks test and log-transformed and/or corrected for outliers when necessary. Descriptive statistics are presented as mean ± standard deviation (SD). Mean differences between groups (HIV positive pregnant women and HIV negative pregnant women) will be done using independent sample t-test. Analysis of variances (ANOVA) will be used to compare continuous variables between three or more groups. Multivariate analysis using multiple analysis of variance (MANOVA) will be used to compare continues variables for two or more independent variables (ART, HIV etc.). Chi-square test will be used to associate cardiovascular risk factors at baseline and follow-up for both mother and child. Pearson correlation will be used to assess relationship between risk factors of CVD. Linear and binomial logistic regressions will be employed to assess the risk of CVDs due to HIV and ART. A confidence interval of 95% will be taken and α = 0.05 will be considered for level of significance.

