The strength of this study relies on the fact that pregnant women (and the foetus) are followed up during pregnancy and thereafter their offspring followed up to investigate the possible epigenetics effect of HIV/ART with regards to cardiovascular risk between mother and offspring. Moreover, the fact that this study combines a wide array of techniques from anthropometric, to non-invasive imaging and ultrasound techniques coupled with measurements of a series of biological markers of cardiometabolic risk factors, vascular function and epigenetics provides a more holistic assessment of cardiovascular risk to attain the desired objectives.

Despite the above strengths of this study, it may be limiting in that: It will be conducted in Mthatha in the Eastern Cape Province of South Africa, a location which is highly dominated by South Africans of African Ancestry. Therefore, the study will mainly constitute South African pregnant women who are of African ancestry. Other ethnic groups within the South African population will not be considered. However, the ethnicity of the children born of these mothers may not be restricted because of the background of their fathers. This study intends to follow-up the children for a period of 24 months which may be too short to sufficiently assess the progression of vascular changes and cardiovascular risk. However, the follow-up period was chosen with respect to the funding period. Presently, the project team is building capacity to attract more funds which can further extend the follow-up period beyond the study duration. A limitation maybe also be that the risk of metabolic syndrome in the offspring may be over-estimated or underestimated when using cut-offs for cardio-metabolic risk from publications from Western world. This will be minimized by ensuring that ethnicity and sex are taken into account when interpreting the results [58–60].

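### The only test tied to follow-up or to the children is a chi-square, which requires continuous risk factors to be cut; used to compare groups, it would have about 44–59% power for a 0.5 SD shift, against 80% uncut

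*Protocol article*

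**What the plan says.** In the protocol article, Statistical analysis, one sentence deals with change over time and with the offspring: "Chi-square test will be used to associate cardiovascular risk factors at baseline and follow-up for both mother and child". A later sentence covers risk: "Linear and binomial logistic regressions will be employed to assess the risk of CVDs due to HIV and ART".

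The same section also names methods that keep the full scale:
- an independent-samples t-test for mean differences between HIV-positive and HIV-negative pregnant women;
- ANOVA for continuous variables in three or more groups;
- MANOVA for continuous variables with two or more independent variables, such as ART and HIV;
- Pearson correlation between risk factors.

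Sample size calculation rests on a standardised mean difference: "An error probability (α) of 0.05, and power (1 − β) of 0.80 and an average effect size (d) of 0.5". It gives 64 per group, raised to 80 for drop-out.

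The Discussion, among its limitations, says that the risk of metabolic syndrome in the offspring "may be over-estimated or underestimated when using cut-offs for cardio-metabolic risk from publications from Western world". It adds that this will be minimised by taking ethnicity and sex into account in interpretation.

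**The concern.** The risk factors are recorded as numbers. Physical/clinical measurements describes BMI, triplicate office blood pressure and 24 h ambulatory blood pressure. Clinical and laboratory investigations describes lipids, urinary albumin and creatinine, and HOMA-IR computed from fasting glucose and insulin. For the children, Study design lists BMI, blood pressure and albuminuria at 3, 6, 12 and 24 months. A chi-square test, like a binomial logistic model, needs these values reduced to present or absent.

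The continuous-scale methods are not assigned to this part of the study. The t-test sentence is confined to the women. The ANOVA sentence is for three or more groups, and the study has two. The regression sentence names linear and logistic models without saying which answers the follow-up question. For the offspring, who are the subject of one of the four objectives, the only test assigned by name is the categorical one.

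The Discussion hopes that the findings will inform guidance on ART in pregnancy and prevention policy for children. If the group comparison at follow-up is made on categories, a shift as large as the study was planned to detect could easily be missed, and the null result read as no added risk.

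**Working it through.** **Inputs from the documents**
- Sample size calculation: α = 0.05, power 0.80, d = 0.5, 64 evaluable per group. Sidedness is not stated; two-sided reproduces the 64.
- Background, general South African population: hypertension 10.2%, insulin resistance 10–20.7%, dyslipidaemia 24%, obesity 20–25%.

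**Assumptions added here**
- The measure is normal with equal SD in both groups.
- The Background prevalences stand in for the control group. They are the only figures in the article from which a cut-point can be placed. None is given for infants.
- The planned shift of 0.5 SD applies to each risk factor.
- The chi-square compares the two HIV/ART groups, 64 in each.

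**Step 1: reproduce the plan's figure.** For a two-sample t-test, the noncentrality is d × √(n/2) = 0.5 × √32 = 2.828, with 126 degrees of freedom and a two-sided critical value of 1.979. Power is 80.1% at 64 per group and 79.5% at 63. So 64 is the exact two-sided t-test figure, and 64 × 1.25 = 80 is the stated recruitment target per group.

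**Step 2: cut the same shift.** If a share p0 of controls lies above the cut-off, the cut-off is at z(1−p0) in control SD units. A shift of 0.5 SD puts the exposed share at p1 = 1 − Φ(z(1−p0) − 0.5). For hypertension, z(0.898) = 1.270, so p1 = 1 − Φ(0.770) = 22.1%.

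**Step 3: power of the two-group chi-square.** Sum the binomial probabilities of all outcome pairs, 64 per group, for which the uncorrected Pearson statistic exceeds 3.841.

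| Control share above cut-off | Exposed share | Background figure it matches | Chi-square power |
|---|---|---|---|
| 10% | 21.7% | insulin resistance, low | 44.0% |
| 10.2% | 22.1% | hypertension | 44.3% |
| 20% | 36.6% | obesity, low | 56.1% |
| 20.7% | 37.6% | insulin resistance, high | 56.5% |
| 24% | 41.8% | dyslipidaemia | 58.4% |
| 25% | 43.1% | obesity, high | 59.0% |
| 50% | 69.1% | none; cut at the control median | 61.4% |

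A normal approximation gives 44.2% at a control share of 10% and 58.0% at 25%, within about one point of the exact values.

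**Step 4: the difference.** Against 80.1% for the t-test, the loss is 80.1 − 59.0 = 21 points to 80.1 − 44.0 = 36 points over the Background prevalences. Even a cut at the control median loses 80.1 − 61.4 = 19 points.

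**The case against.** The strongest reply is that the 80% belongs to a two-sample t-test, which the plan keeps for the women. The sample size is drawn from studies of vascular function, not of hypertension or obesity status. A reader might infer from the table that the study's 80% power falls to 44–59%. The documents do not support that: nothing says the powered maternal comparison will be cut.

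A reader might also infer that all continuous measures are to be dichotomised. That does not follow either. ANOVA, MANOVA, correlation and linear regression are all named, log-transformation is planned, and results are described as mean ± SD. Hypertension and obesity are recognised diagnoses, and tabulating them as categories is ordinary practice.

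The chi-square sentence is also open to a second reading, in which it relates a person's baseline status to the same person's follow-up status. Those data are paired, and the two-group formula above would not describe that test. This limits the power figures to the between-group reading. It does not remove the point: the values would still have to be cut, and such a test would not compare the HIV/ART groups, so the follow-up group question would have no test assigned to it by name.

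The Background prevalences are for the general population. This cohort has uncomplicated pregnancies, with diabetes, renal disease and CVD excluded, and the cases are under 35. Its true prevalences may differ, so the range is illustrative.

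Finally, it would be too strong to say that the authors regard the offspring cut-offs as unreliable. They say that Western cut-offs may bias the estimated risk in either direction, and they offer a mitigation. That mitigation acts at interpretation, however, and leaves the test itself dependent on the cut-offs.

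**Conclusion.** The point holds in a limited form. The only analysis sentence that names follow-up or the child prescribes a test that needs categories, although the measures are continuous and the plan already contains suitable full-scale methods that it does not assign to these comparisons.

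If the HIV/ART groups are compared at follow-up by chi-square, power for a 0.5 SD shift at 64 per group is about 44–59%, against 80% on the continuous scale. That range is conditional on a between-group reading, normal measures with equal SD, and control prevalences of 10–25%. The maternal t-test keeps its 80%. The change should be made because the loss is avoidable, and because in the offspring it removes the inferential test's dependence on cut-offs of doubtful fit.

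**What to change.** In Statistical analysis, replace the chi-square sentence with a statement that:
- risk factors at baseline and at follow-up, in mothers and in children, will be compared between the HIV/ART groups on their continuous scale by linear models;
- skewed measures will be log-transformed, and children's BMI and blood pressure will be standardised for age and sex;
- repeated visits of the same person will be handled as correlated, for example by a mixed model;
- results will be reported as group mean differences (ratios for log-transformed measures) with 95% confidence intervals.

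Then state that proportions above cut-offs, and any chi-square or logistic results on them, are supportive. In the regression sentence, say that the linear model on the continuous measure carries the inference.

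This rewords two sentences and needs no new data, visits or participants. The small downside is that clinical readers will want proportions, so these must be tabulated beside the mean differences.

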Globally, over 1.4 million pregnant women are living with HIV [29]. Among this population, about 960,000 HIV-infected pregnant women reside in Eastern and Southern Africa. In South Africa, 30.2% of all pregnant women who attended public health-care facilities in 2012 were infected with HIV [30]. The risk of CVD is becoming more prevalent in pregnant women [31] though not much attention has been paid to this population. Gestational diabetes mellitus (GDM) is associated with macro and microvascular endothelial dysfunction of the placenta mainly triggered by hyperinsulinemia, hyperglycaemia, and changes in nucleoside extracellular concentration [32].

Endothelial dysfunction may alter the intrauterine environment of the foetus. Foeto-placental vascular endothelial dysfunction may cause epigenetic alteration in the intrauterine environment of the foetus. This may be the origin of chronic diseases such as diabetes and obesity in childhood predisposing children to CVDs which may track into adulthood [33]. According to the concept of the Developmental Origins of Health and Disease, the maternal environment/gestational milieu may have a significant impact on the health of the offspring in adulthood and may be responsible for programming children for CVDs later on in life [34]. Indeed, poor placental perfusion as in pre-eclampsia has been associated with preprograming for obesity, hypertension and diabetes in adult life [35]. Animal studies have shown that administration of combination ART during pregnancy was associated with poor placental insertion and development resulting in growth restricted offspring [36]. Because HIV infection and ARTs are associated with increased cardiovascular risk factors including endothelial dysfunction, we hypothesize that HIV-infection/ARTs will promote endothelial dysfunction which will engender poor placental perfusion resulting in offspring being pre-programed for increased cardiovascular risk later on in life.

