## Methods/design

### Aim and objectives

The aim of this study is to investigate whether HIV-infection and ART are associated with risk of cardiometabolic diseases in pregnant women of African ancestry and their offspring after birth. This study aims to:Assess cardiometabolic disease risk in HIV positive pregnant women on ART and HIV negative pregnant women.Determine foetal health in the maternal HIV/ART environment during the three trimesters of gestation.Assess cardiometabolic health of mothers exposed to HIV/ART at various time points after delivery.Assess cardiometabolic risk in offspring of HIV positive mothers who were on ART during pregnancy at birth at predetermined time points after birth.

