The ARTMOMSBABES study is an important study in the South African context as there is evidence of increasing prevalence of cardiovascular risk in children without a clear understanding of the underlining cause. This study may be able to address this concern by first assessing cardiometabolic risk and vascular changes in HIV-infected pregnant women on ART and then follow-up their offspring after birth for possible cardiovascular risk as a result of in utero exposure. The finding may contribute to develop guidelines in the management of ARTs used in pregnant women and cardiovascular risk in children. The biomarkers analysed will be helpful to understand the molecular determinants of vascular endothelial changes in pregnancy that may promote the development of cardiovascular risk in children. More so, the findings of this study may start the process of unravelling the mechanism behind the increased prevalence of cardiovascular risk factors observed in children of African ancestry.

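### Correlations between risk factors are planned without regard to HIV/ART group, so shared exposure can pass for a link between markers

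*Protocol article*

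**What the plan says.** The Background of the protocol article states its hypothesis as a sequence: "we hypothesize that HIV-infection/ARTs will promote endothelial dysfunction which will engender poor placental perfusion resulting in offspring being pre-programed for increased cardiovascular risk". The Discussion returns to mechanism: "The biomarkers analysed will be helpful to understand the molecular determinants of vascular endothelial changes in pregnancy". The formal aim, under Aim and objectives, is associational: to "investigate whether HIV-infection and ART are associated with risk of cardiometabolic diseases in pregnant women of African ancestry and their offspring after birth".

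The Statistical analysis section assigns methods by type of question:

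- **Exposure against an outcome.** "Mean differences between groups (HIV positive pregnant women and HIV negative pregnant women) will be done using independent sample t-test". ANOVA and MANOVA are also named, and "Linear and binomial logistic regressions will be employed to assess the risk of CVDs due to HIV and ART".
- **Risk factors at baseline and follow-up.** Chi-square test.
- **Continuous risk factors against one another.** "Pearson correlation will be used to assess relationship between risk factors of CVD". Nothing is said about adjusting for HIV/ART group or stratifying by it.

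The Sample size calculation uses "An error probability (α) of 0.05, and power (1 − β) of 0.80 and an average effect size (d) of 0.5", "based on previously published studies in which vascular function was assessed in HIV patients". It gives 64 per group, raised to 80 per group for 25% dropout: 160 mothers and 160 offspring.

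**The concern.** The t-test, MANOVA and regressions cover HIV/ART against each measured variable. They do not cover one marker against another, and the second and third steps of the hypothesised sequence are of that kind. For those steps the only named tool is a simple correlation.

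The sample is half exposed and half unexposed by design, and the hypothesis is that exposure moves maternal, placental and offspring measures. If exposure moves two of them by separate routes, the two group clouds sit apart on both axes. A correlation over all pairs then picks up that separation, even when the markers are unrelated within either group. A reader could take it as evidence that maternal endothelial change is passed on to the child, when it only restates that both differ by HIV/ART status. The protocol lists many markers, so many such correlations are possible.

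**Working it through.** **Plan's own figure.** For d = 0.5, two-sided α = 0.05 (sidedness is not stated; two-sided assumed) and a t-test, 64 per group gives 80.1% power, so the stated 64 reproduces. 64 × 1.25 = 80. A 25% loss from 80 leaves 60 per group, or N = 120 mother-child pairs, which is used below.

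**Inputs.** d = 0.5 is the plan's. Shifts of 0.8 and 1.0, and all link correlations, are assumptions, because the protocol gives none. Within-group SDs are set to 1.

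**Correlation created by group alone.** With equal groups, no link within group, and shifts d₁ and d₂ in the two markers:

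r = (d₁d₂/4) / √[(1 + d₁²/4)(1 + d₂²/4)]

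For d₁ = d₂ = d this is (d²/4)/(1 + d²/4):

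- d = 0.5: 0.0625/1.0625 = 0.059
- d = 0.8: 0.16/1.16 = 0.138
- d = 1.0: 0.25/1.25 = 0.200

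**False-positive rate of the pooled test.** By Fisher's z, with δ = atanh(r) × √(120 − 3), the rate is Φ(δ − 1.96) + Φ(−δ − 1.96):

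| Shift in both markers | r | δ | Pooled, formula | Pooled, simulated | Adjusted for group, simulated |
|---|---|---|---|---|---|
| 0.5 | 0.059 | 0.64 | 9.8% | 9.7% | 5.0% |
| 0.8 | 0.138 | 1.50 | 32% | 33% | 5.0% |
| 1.0 | 0.200 | 2.19 | 59% | 60% | 4.9% |

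The simulation used 10,000 runs per row.

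**Small child shift.** With d₁ = 0.5 in the mother and d₂ = 0.2 in the child, r = 0.025/√(1.0625 × 1.01) = 0.024 and δ = 0.26. The rate is Φ(−1.70) + Φ(−2.22) = 4.5% + 1.3% = 5.8%, which is close to nominal.

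**Power when the link is real.** Take d = 0.5 on the maternal marker, a within-group mother-child correlation r, no direct effect and 60 per group. Require both the group t-test on the marker and the marker-to-child test to be significant:

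| r | Marker-to-child by pooled Pearson | Marker-to-child adjusted for group |
|---|---|---|
| 0.2 | 49% | 46% |
| 0.3 | 73% | 71% |
| 0.4 | 78% | 78% |

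These come from 4,000 simulation runs; repeat runs differ by one or two percentage points. A single pooled Pearson test at N = 120 has 59%, 92% and 99.6% power at r = 0.2, 0.3 and 0.4.

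**The case against.** **The text does not say that groups will be pooled.** Within-group correlation fits the same sentence and would remove the problem. An article may also leave such detail to a fuller plan. This is fair, and it limits the point. But the article does name the method and names no other for these relationships. Read plainly, a Pearson correlation between risk factors is a simple one over the sample, so a clarifying sentence is warranted.

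**At the plan's only effect size the inflation is modest.** This stands: about 10% instead of 5%, and only if the second marker also shifts by 0.5. The larger figures rest on assumed shifts.

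**Mediation is not an objective.** This also stands. The aims are associational, and the t-tests, MANOVA and regressions address them. The lack of a mediation model is not a fault here.

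**A stronger reading is tempting:** that reliance on Pearson correlation makes a true chain nearly undetectable, so that the hypothesis can be neither supported nor refuted. The figures do not bear this out. Pooled Pearson detects moderate links well and is slightly more powerful than the adjusted test. What has low power is the child comparison between HIV groups. If the effect runs only through one intermediate marker with r = 0.2, 0.3 or 0.4, the child difference is 0.5 × r = 0.10, 0.15 or 0.20 SD, and power at 60 per group is 8%, 13% or 19%. That is dilution at this sample size under an assumption of no direct effect, which the protocol does not make. Changing the correlation method would not alter it.

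**Conclusion.** The concern holds in a limited form. Links between continuous markers, including the later steps of the Background hypothesis, are left to a correlation for which no account of HIV/ART group is stated. Pooled over an exposed and an unexposed group of equal size, that correlation cannot separate a real link from shared exposure.

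The false-positive rate is about twice nominal at d = 0.5 in both markers, about 33% and 60% at assumed shifts of 0.8 and 1.0, and near nominal when the child shift is small. These figures assume 60 pairs per group, equal group sizes, unit within-group SDs, linear relations, a two-sided 5% test and pooling. If the correlations are meant to be within group, only the wording needs attention.

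This is a matter of validity for the marker-to-marker analyses. It does not touch the planned group contrasts or the associational aims.

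**What to change.** In the Statistical analysis section, state that correlations between risk factors, including those pairing maternal, placental and child measures, will be adjusted for HIV/ART group or reported separately within each group. Adjustment can be by partial correlation or by linear regression with group in the model.

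No new data are needed. Adjustment costs one degree of freedom and a little power (46% against 49% for the two-step test at r = 0.2). Reporting within group costs more precision, because each estimate then rests on about 60 pairs.

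A formal indirect-effect estimate could be added as exploratory, with its assumption of no unmeasured confounding stated. The aims do not require it.
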